### Balance rehabilitation

Balance is complex, relying on integration of vestibular, visual and somatosensory inputs for postural orientation and motion while central processes monitor and control the interaction between musculoskeletal and neural systems to generate anticipatory postural adjustments and adapt posture to changing environmental and balance task demands.^1423^,^25^ Previous studies have indicated that multisensory balance rehabilitation (MBR) can improve dynamic balance.^23^,^27^ MBR consists of exercises that aim to improve balance, gait, somatosensory integration and gaze stability through compensation, adaptation, habituation and/or substitution of the vestibular ocular reflex and/or vestibulospinal reflex.^28^,^30^ Multisensory exercises, consisting of activities simultaneously stimulating at least two sensory modalities, including visual, auditory, tactile, vestibular and somatosensory systems, are effective for improving balance in people with balance disorders.^24^ MBR programmes which address balance have shown substantial reduction in falls risk in older adults, compared with standard programmes.^231^,^33^

Balance rehabilitation is the most effective treatment for balance disorders across all ages, typically involving personalised exercises prescribed by healthcare professionals.^21 34 35^ However, access to specialist services is often limited due to resource and staffing constraints. While effective in reducing fall risks among older adults, balance/falls programmes face challenges such as poor adherence, with up to 50% of participants dropping out early.^3436^,^38^ Common limitations include inadequate exercise progression, lack of individualisation and minimal supervision, and they often fail to address real-world situations such as dual-task training or activities simulating everyday challenges (eg, crossing a road).^1734 36^,^38^

Studies concerning the effect of MBR on balance and gait outcomes among stroke survivors, MCI, vestibular dysfunction and long covid are limited,^27^ and even in persons with vestibular dysfunction where multiple studies exist, optimal treatment strategies are still unknown.^9 21 39 40^ Balance rehabilitation programmes are rarely multisensory and commonly lacking a cognitive element, which are key factors in addressing static and dynamic balance.^17 41 42^ Further research is needed to investigate the optimal MBR for these populations.^43^

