Participants will be required to complete the programme 5 days per week over 9 weeks. They will be encouraged to complete the programme in one session per day, but if required due to fatigue and/or scheduling issues, may complete the session in multiple bouts within a 24-hour period. Participants will be required to wear the equipment when performing the prescribed exercises. At the end of the study, a subset of participants will be invited to participate in a semistructured exit interview to discuss their experience using the TeleRehaB DSS system. This qualitative feedback on acceptability and usability will help to inform future iterations of the platform, for a larger-scale RCT and eventual adoption into local healthcare systems.

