### Outcome measures

All study participants will attend two sessions at the clinical site: at baseline (week 0) and post-intervention (week 10), where a blinded outcome assessor will collect outcome measure data. Participants will be asked to complete a subjective questionnaire set, walking/balance tests, a verticality perception test and a cognitive screen. These will take approximately 1.5 hours, including comfort breaks. Participants’ e-health literacy will only be collected at baseline, while system usability score (SUS) and User Experience Questionnaire (UEQ) will be collected post-intervention among the IG only.

The outcome assessor will be asked to record any incidences of unblinding and detail how this occurred. Due to the nature of this study, we do not foresee circumstances where emergency unblinding of the outcome assessor is required.

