#### Primary outcome measures

Primary outcomes of feasibility, acceptability, usability and safety will be investigated alongside clinical measures of Functional Gait Assessment (FGA) and EuroQol five-dimensional descriptive system (EQ-5D-5L) instrument pre-intervention and post-intervention. The FGA includes 10 tasks that assess dynamic and complex gait (eg, walking with head turns or stopping and turning), with a minimal detectable change (MDC) of 4.2 points in stroke populations and 6 points in vestibular disorders^61^ and minimally clinically important difference (MCID) of 4 points in community-dwelling older adults.^62 63^

Programme effectiveness will be evaluated using quality-adjusted life years (QALYs) measured with the EQ-5D-5L instrument.^64^ The EQ-5D-5L is a standardised, valid and reliable measure of health status for clinical and economic appraisal.^64^ The respondent is asked to rate their health status on five dimensions (mobility, self-care, usual activities, pain/discomfort, anxiety/depression), followed by a self-rated health score from 0 to 100. MCID ranges from 0.03 to 0.52.^65^,^67^

Primary outcomes are as follows:

*Acceptability*: recruitment (percentage of eligible participants enrolled); dropout rates; intervention adherence (percentage of prescribed sessions completed) monitored automatically through the system for TeleRehaB DSS participants and via an exercise diary for control groups.*Safety*: participants will be monitored for adverse event’s via completion of adverse events forms on the system database, during telephone or face-to-face contacts as part of the intervention phase and during follow-up assessments. Falls diaries will be collected weekly from participants during the intervention, and monthly for up to 6 months after completion of the intervention.*Feasibility*: protocol deviation (PD) or study protocol implementation problems (eg, logistical).*Usability*: participants’ experience using the system (perceived benefits, frustrations and recommendations) will be explored via exit interviews for all TeleRehaB DSS group completers. These participants will also complete the SUS^68^ and UEQ^69^ to explore system usability and user experience, respectively.

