#### Usability and acceptability

System effectiveness and user satisfaction with TeleRehaB DSS will be assessed by comparing predicted versus observed outcomes, with SUS and UEQ scores providing usability and user experience feedback.

Participants in the TeleRehaB DSS intervention group will be invited to provide qualitative feedback through exit interviews. Questions will cover user satisfaction, perceived effectiveness of TeleRehaB DSS and any challenges faced. Recorded and transcribed interviews will be analysed to identify recurring themes related to the ease of use, perceived benefits and any barriers to engaging with the system. Feedback from exit interviews will also be reviewed for insights into potential system improvements, such as interface usability, feature enhancements and suggestions for additional support or training.

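### Usability is a primary outcome, but its scores and interviews come from undefined completers at week 10, so people who stop early and miss that visit contribute nothing to it

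*Protocol article*

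**What the plan says.** Under Primary outcome measures, the article opens with "Primary outcomes of feasibility, acceptability, usability and safety will be investigated alongside clinical measures". The usability item then says that experience with the system "will be explored via exit interviews for all TeleRehaB DSS group completers", and continues "These participants will also complete the SUS" and the UEQ. Read literally, all three usability instruments belong to completers of the TeleRehaB DSS arms. The article does not say what makes a participant a completer.

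The timing is the same throughout. The Outcome measures section says the SUS and UEQ "will be collected post-intervention among the IG only". Table 2 places the SUS, UEQ and exit interviews in the week 10 column and nowhere else. No section provides for collecting them when a participant stops.

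Who is interviewed is described in three ways:

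- **Primary outcome measures:** all completers in the intervention group.
- **Intervention group section:** at the end of the study, "a subset of participants will be invited to participate in a semistructured exit interview".
- **Usability and acceptability section:** "Participants in the TeleRehaB DSS intervention group will be invited to provide qualitative feedback through exit interviews", with no completer limit.

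Dropout and adherence are recorded, but as parts of the acceptability outcome.

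**The concern.** The usability outcome is meant to bring out frustrations and recommendations as well as benefits, and the interview analysis is to look for barriers to engagement. People who give up on the headset, sensors or tablet are well placed to report those barriers. A rule that takes usability data only from completers at the final visit selects on staying in, and staying in may itself depend on how usable the system is.

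The article recognises that route: its list of limitations says self-setup and home use of the technology may affect adherence and data completeness. The stated aims are to refine the platform and to supply preliminary data for a definitive trial. A usability summary that leaves out those who stopped would give that trial too favourable a starting point. Scores that were never collected cannot be recovered in the analysis.

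**Working it through.** **Step 1. Does the text exclude early stoppers?** Set side by side:

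| Section | Who gives usability data | When |
|---|---|---|
| Outcome measures | Intervention group (SUS, UEQ) | Post-intervention |
| Primary outcome measures | Completers (interview, SUS, UEQ) | Exit |
| Table 2 | Not restricted by arm in the table | Week 10 only |
| Intervention group | A subset (interview) | End of study |
| Usability and acceptability | Intervention group invited (interview) | Exit |

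The completer limit is explicit in one section only. The single time point is common to the SUS and UEQ wherever they are scheduled. So even on the wider wording, someone who stops and does not attend week 10 gives no score, and no section arranges an interview for that person.

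**Step 2. How many people might this be?** The article gives no planned dropout for this trial and no total for the intervention group. The target is 460, with 60–100 per site. Five sites give 5 × 60 = 300 to 5 × 100 = 500, so 460 lies inside the range. The intervention and control groups have the same stated range per site (30–50), so I assume an equal split: 460 / 2 = 230 in the intervention group.

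**Step 3. What is the bias in the mean?** Let d be the share of intervention participants without usability data, C the mean score in completers and N the mean the others would have given.

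- Mean over all users = (1 − d) × C + d × N
- Completer mean minus all-user mean = C − [(1 − d) × C + d × N] = d × (C − N)

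**Step 4. Put in numbers.** The values of d are assumptions. The upper one, 50%, is borrowed from the background section, which reports poor adherence in balance and falls programmes "with up to 50% of participants dropping out early". The gap C − N is also assumed, in SUS points.

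| d | With data (of 230) | Without data | Gap 0 | Gap 5 | Gap 10 | Gap 20 |
|---|---|---|---|---|---|---|
| 10% | 207 | 23 | 0 | 0.5 | 1 | 2 |
| 20% | 184 | 46 | 0 | 1 | 2 | 4 |
| 30% | 161 | 69 | 0 | 1.5 | 3 | 6 |
| 50% | 115 | 115 | 0 | 2.5 | 5 | 10 |

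For example, 0.3 × 20 = 6 points. Across the non-zero gaps the overstatement runs from 0.1 × 5 = 0.5 to 0.5 × 20 = 10 points. The same identity holds for any UEQ mean on its own scale.

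**The case against.** The strongest reply has four parts.

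1. **The completer limit is not consistent.** It stands in one section; Outcome measures and Usability and acceptability describe the intervention group without it. Completer is undefined and all participants are expected at week 10, so someone who abandoned the equipment but attended could be counted. This stands. A reader might infer that everyone who gave up on the equipment is excluded, but the article does not say so. The exclusion is certain only for those who do not reach week 10.

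2. **Information on stopping is collected elsewhere.** Weekly calls and the week 3 and 6 reviews cover technical problems, device deficiencies are reported, the participant flow diagram records reasons for discontinuation, and dropout and adherence are primary outcomes in their own right. This also stands. It tells the reader how many stop and broadly why. It supplies no SUS or UEQ score and no interview from them.

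3. **The size does not come from this trial.** The 50% figure describes other programmes and is not a planning assumption, and the gap in scores is assumed. People who stop for unrelated reasons would add little bias. A reader might infer that usability is overstated by a known amount, or overstated for certain. Neither follows.

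4. **This is a feasibility study and an article.** No usability threshold or progression rule is stated that a biased mean could cross, and details of withdrawal are often left to a full protocol. That limits the consequence. It does not answer the point, which concerns a rule the article itself states about who supplies data for a primary outcome.

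A reader might also infer that a usability comparison of the high-tech and low-tech arms would be distorted. The article states no such comparison, so that is not part of this point. Should one be made, unequal dropout between the arms would matter.

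**Conclusion.** The point holds in a limited form. As written, usability data come from completers at week 10, and intervention participants who stop early and miss that visit provide none. If they find the system harder to use, which is plausible but not shown, the usability summary is likely to be too favourable by d × (C − N). The article does not allow that to be estimated. The illustration of 0.5–10 SUS points rests on assumed non-completion of 10–50% and an assumed gap of 5–20 points, and the bias is zero if there is no dropout or no gap.

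Separately, and whatever the bias, the article disagrees with itself on whether all completers, a subset of participants or intervention group participants generally are interviewed. A primary outcome is affected, so both matters should be put right, but neither bears on participant safety.

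**What to change.** - Define the usability set as all intervention group participants who had the system installed, and summarise the SUS and UEQ on that set.
- When someone stops early, offer the SUS, the UEQ and an interview invitation at the existing weekly call or when the equipment is removed.
- Report how many in the set have no usability data, with reasons, and show the summary again under a range of assumed gaps for those missing. Keep the completers-only figure as a secondary summary.
- Define completer, stating whether it refers to use of the system or to attendance at week 10.
- Reconcile the Intervention group, Outcome measures, Primary outcome measures, and Usability and acceptability sections on who gives scores and who is interviewed. If only a subset is interviewed, say how it is drawn and include people who discontinued.

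The cost is a few extra short questionnaires and interviews within contacts already planned. Some who stop will decline, so the selection is reduced, not removed, and the response among them should be reported.

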#### Secondary outcome measures

Various secondary outcome measures will be used to assess clinical outcomes, programme effectiveness, system performance, AI model predictive power, e-health literacy and user experience. Please see table 2 for the detailed schedule of assessments.

**Table 2 T2:** Schedule of assessments for all participants enrolled in the TeleRehaB DSS study

		Screening	Baseline	Week 0	Weekly	Weeks 3 and 6	Post-intervention (week 10)	Monthly
Recruitment procedures	PIS informed consent	X	X					
Data collection and outcome measures	Demographics		X					
	HADS	X					X	
	DHI	X					X	
	FGA	X					X	
	MoCA	X					X	
	EQ-5D-5L		X				X	
	RAPA		X				X	
	ABC		X				X	
	Mini-BESTest		X				X	
	SVV		X				X	
	WEMWBS		X				X	
	FSS		X				X	
	SVQ		X				X	
	Exit interviews						X	
User experience measures	SUS						X	
	UEQ						X	
eHealth literacy measures	eHEALS		X					
	STAM-14		X					
	MDPQ-s		X					
Home-based interactions	Equipment installation and practice session (*IG only*)			X				
	Equipment de-installation (*IG only*)						X	
	Telephone call				X			
	Remote programme review					X		
	Perform HEP				X			
	Submit falls diary				X			X
	Submit exercise log				X			

ABC, Activities Specific Balance Confidence Scale; DHI, Dizziness Handicap Inventory; eHEALS, eHealth Literacy Assessment; EQ-5D-5L, EuroQol five-dimensional descriptive system; FGA, Functional Gait Assessment; FSS, Fatigue Severity Scale; HADS, Hospital Anxiety and Depression Scale; HEP, home exercise programme; IG, intervention group; MDPQ-s, Mobile Device Proficiency Questionnaire - short; Mini-BESTest, Mini-Balance Evaluation Systems Test; MoCA, Montreal Cognitive Assessment; PIS, Participant Information Sheet; RAPA, Rapid Assessment of Physical Activity; STAM, Senior Technology Acceptance and Adoption Model-14; SUS, System Usability Scale; SVQ, Situational Vertigo Questionnaire; SVV, Subjective Visual Verticality; TeleRehaB DSS, TeleRehabilitation Decision Support System; UEQ, User Experience Questionnaire; WEMWBS, The Warwick-Edinburgh Mental Wellbeing Scale.

Cost-effectiveness by means of the incremental cost-effectiveness ratio (ICER; the difference in mean costs divided by the difference in mean QALYs at the time of recruitment to the study and 1 year before the study and 1 year after the end of the intervention).

Objective measures include the Mini-Balance Evaluation Systems Test^70^ (mini-BESTest) to assess complex gait and dynamic balance tasks, the Montreal Cognitive Assessment (MoCA)^71^ as a measure of cognitive function, and the Subjective Visual Verticality (SVV)^72 73^ to evaluate a person’s perception of verticality. The mini-BESTest is a 14-item test that assesses static and dynamic balance, with a MDC of 3.5 and MCID of 4 points for balance/vestibular disorders^74^ and 5.52 points’ MDC in neurological conditions.^75^ The MoCA assess visuospatial/executive function, naming, attention, language, abstraction, memory and orientation to time and place, with a MDC of 4 points among older adults.^76^ SVV evaluates a person’s perception of verticality using a ‘rod and disk’ programme delivered on the computer, where the subject is asked to adjust a visual line to what they perceive as vertical. It is commonly used to diagnose and assess vestibular function.^72 73^

Subjective questionnaires include the Dizziness Handicap Inventory, a 25-item questionnaire which measures dizziness disability, with a MDC of 17.18 points and MCID of 18 points for balance/vestibular disorders;^77^ Activities-Specific Balance Confidence Scale,^78^ a 16-item questionnaire assessing balance confidence in varying situations, with a MDC of 14.89 in older adults,^79^ MDC of 19.79 points and MCID from 30.93 to 49.56 in stroke^80^ and MCID of 18 points in balance/vestibular disorders;^81^ Rapid Assessment of Physical Activity,^82^ a 9-item questionnaire to broadly assess physical activity levels; the Hospital Anxiety and Depression Scale,^83^ a 14-item scale which assesses anxiety and depression symptoms with an MDC of 4.66 and MCID of 1.17–2.13 for the anxiety subscale and MDC of 4.43 and MCID 1.48–2.54 for the depression subscale among patients with chronic pain;^84^ Fatigue Severity Scale,^85^ a 9-item instrument designed to measure fatigue, with a MDC of 1.9 points in multiple sclerosis,^86^ which will only be administered to the long covid cohort; the Warwick-Edinburgh Mental Wellbeing Scale,^87^ a 14-item scale assessing mental well-being; and the Situational Vertigo Questionnaire,^88^ a 20-item scale for assessing the impact of disorienting environments.

E-health literacy will be measured at baseline only, using the eHealth Literacy Assessment^89^ to evaluate patients’ skills in finding, evaluating and applying electronic health information; the Senior Technology Acceptance and Adoption Model-14^90^ to measure factors influencing technology acceptance among older adults; and the Mobile Device Proficiency Questionnaire - short,^91^ a highly reliable and valid measure of mobile device proficiency.

### Data management and analysis

#### Statistical analysis

Anonymised data will be entered into a study database. Data integrity will be assessed by taking a random 10% sample of entries following completion of data collection. The rectified database will be saved under a new filename (eg, study database_rectified_date) and all changes made to the database will be logged. All essential trial documentation will be saved on the dashboard except for the consent form which will be saved at each clinical site in paper form. The sponsor will ensure that study documentation is retained in accordance with their local approvals after the conclusion of the trial.

As this is a feasibility study, there is no formal plan for statistical analysis. However, for a future trial, an analysis plan has been developed which will be run in this study to determine its appropriateness. Descriptive statistics will be used to summarise feasibility outcomes of adherence, compliance and dropout rates. Continuous secondary outcome measures will be reported as means with 95% CIs.

Normality of outcome variables will be assessed by visual inspection and appropriate statistical tests. Where assumptions of normality are met, intention-to-treat analyses will be conducted using repeated-measures general linear model analysis of variance to explore between-group and within-group trends, adjusting for clinical site and cohort. Where normality assumptions are not met, non-parametric alternatives will be employed, including Wilcoxon signed-rank tests for within-group comparisons, Mann-Whitney U test for between-group comparisons and Friedman tests for repeated measures where appropriate.

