**Methods and analysis:**

This multicentre, assessor-blinded randomised controlled trial will recruit 460 community-dwelling adults aged 40–80 years with stroke, MCI, vestibular dysfunction or long covid across five sites in the UK, Europe and Southeast Asia. Participants will be randomised to a 9-week remotely supervised home exercise programme using either TeleRehaB DSS (high-tech or low-tech MBR with exergames and cognitive training) or standard care (OTAGO home exercise programme or Meniere’s Dizziness booklet). Primary outcomes include feasibility, acceptability and safety, alongside clinical measures of balance and health-related quality of life (Functional Gait Assessment, EuroQol five-dimensional descriptive system instrument). Secondary outcomes assess balance, cognition, physical activity, dizziness, psychological well-being, fatigue and confidence. Usability, user experience and digital health literacy will also be evaluated. Anonymised data will undergo quality checks and be analysed using descriptive and exploratory statistics, mixed-effects models, cost-effectiveness analysis (incremental cost-effectiveness ratio) and thematic analysis of qualitative interviews, adjusting for site and relevant confounders.

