**Figure 2 F2:**
[figure not shown]
CONSORT diagram to demonstrate participant flow through the TeleRehaB DSS RCT. After baseline testing and randomisation, participants were allocated to either the intervention group, comprising a high-technology arm and low-technology arm, or the control group. The control group consisted of participants receiving either the OTAGO HEP or a vestibular-specific HEP. Assessments were conducted at baseline, week 3 (review 1), week 6 (review 2) and week 10 (final assessment). Participant numbers, dropouts and reasons for loss to follow-up or intervention discontinuation were recorded at each stage. Final analysis was performed according to group allocation, noting any exclusions. CONSORT, Consolidated Standards of Reporting Trials; HEP, home exercise programme; RCT, randomised controlled trial; TeleRehaB DSS, TeleRehabilitation Decision Support System.

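### The planned repeated-measures ANOVA is labelled intention-to-treat, but with two visits it compares unadjusted mean change among participants who have both, and it is open to bias if missing week-10 data depend on baseline function differently by arm

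*Protocol article*

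**What the plan says.** All references are to the protocol article.

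- **Model and label (Statistical analysis).** Where normality holds, "intention-to-treat analyses will be conducted using repeated-measures general linear model analysis of variance", with adjustment for site and cohort. Baseline value is not listed as a covariate. Where normality fails, the fallback is "Wilcoxon signed-rank tests for within-group comparisons, Mann-Whitney U test for between-group comparisons and Friedman tests for repeated measures where appropriate".
- **Visits (Outcome measures).** "All study participants will attend two sessions at the clinical site: at baseline (week 0) and post-intervention (week 10". The sentence covers all participants and is not limited to those still exercising.
- **Clinical measures (Primary outcome measures).** The feasibility outcomes are studied alongside "clinical measures of Functional Gait Assessment (FGA) and EuroQol five-dimensional descriptive system (EQ-5D-5L) instrument pre-intervention and post-intervention". Table 2 shows one reading of each before the programme and one at week 10.
- **Mixed models.** The abstract says data will be "analysed using descriptive and exploratory statistics, mixed-effects models". In the body, the mixed-effects model is specified for QALYs and costs, with baseline health among its adjusters.
- **Status of the analysis.** The trial is described as not powered for effectiveness and as having no formal analysis plan. The same section adds that the analysis was developed for a future trial and is being run here to judge whether it is appropriate.

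**The concern.** An intention-to-treat analysis takes everyone randomised, in the allocated arm. A two-visit repeated-measures ANOVA, as ordinarily fitted, takes only those with both readings. A participant with no week-10 value contributes nothing, and the baseline value is lost too. The rank-test fallback has the same limit. Signed-rank and Friedman tests need complete sets, and Mann-Whitney on week-10 or change values needs week 10.

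The second issue is statistical. A difference in mean change does not condition on the baseline value. If people with poorer baseline gait are likelier to miss week 10 in one arm than in the other, the remaining participants differ at baseline between arms, and regression to the mean then enters the treatment contrast. Differential missingness is plausible here because one arm uses a headset, body sensors and a camera and the other a booklet and a diary. The strengths and limitations list itself warns that home use of technology may affect data completeness.

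At stake are the effect estimates that the article says will inform sample size for the definitive trial, and the choice of model for that trial.

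**Working it through.** **No stated figure to reproduce.** The target of 460 rests on a per-site feasibility range (5 × 60 = 300 to 5 × 100 = 500), not on a power calculation. The article gives no SD, correlation, effect size or expected dropout. The values below are assumptions.

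**Step 1: who is analysed.** Number with both visits = 460 × (1 − d), where d is the proportion without week 10.

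| d | analysed | left out |
|---|---|---|
| 10% | 414 | 46 |
| 20% | 368 | 92 |
| 30% | 322 | 138 |

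**Step 2: what the ANOVA estimates.** With two time points, the group-by-time term is

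(mean change in intervention) − (mean change in control), among those with both visits.

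Let r be the baseline-to-week-10 correlation, with equal SDs, and let S be the amount by which the mean baseline of retained intervention participants exceeds that of all randomised to that arm. If control dropout is random,

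expected contrast = true effect − (1 − r) × S.

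**Step 3: numbers.** Assumptions: SD 5, r = 0.6, true effect 2 points, 230 per group, control dropout 15% at random, intervention dropout 30% with logistic dependence on baseline (lower function, more dropout).

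| Log-odds of dropout per SD of lower baseline | S (points) | ANOVA contrast | Baseline-adjusted |
|---|---|---|---|
| 1 (strong) | 1.26 | 2 − 0.4 × 1.26 = 1.49 | 2.0 |
| 0.5 | 0.71 | 2 − 0.4 × 0.71 = 1.71 | 2.0 |
| 0.25 | 0.37 | 2 − 0.4 × 0.37 = 1.85 | 2.0 |
| 0 (none) | 0 | 2.00 | 2.0 |

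Simulation agrees with both columns. With strong selection, r = 0.5 gives 2 − 0.5 × 1.26 = 1.37 and r = 0.7 gives 2 − 0.3 × 1.26 = 1.62.

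The baseline-adjusted figures come from regressing week 10 on arm and baseline in exactly the same retained participants. The bias therefore comes from not conditioning on baseline, not from the smaller analysis set.

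**Step 4: precision without any selection.** Retained: 230 × 0.70 = 161 and 230 × 0.85 = 195.5. √(1/161 + 1/195.5) = 0.1064.

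- Change score: SD = 5 × √(2 − 2 × 0.6) = 4.47; SE = 4.47 × 0.1064 = 0.48.
- Baseline-adjusted: SD = 5 × √(1 − 0.6²) = 4.00; SE = 4.00 × 0.1064 = 0.43.

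The variance ratio is 0.80/0.64 = 1.25.

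**Step 5: effect on planning.** Required sample size scales with 1/effect². Planning on 1.5 rather than 2.0 multiplies it by (2.0/1.5)² = 1.78; planning on 1.71 multiplies it by 1.37.

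**Step 6: limit of the remedy.** In a separate simulation (SD 4, r = 0.6, true effect 0, 20% missing per arm), dropout in one arm depended on the unseen change. The ANOVA contrast was then off by 1.00 and the baseline-conditioned estimate by 0.83. Conditioning on baseline does not cure that kind of missingness.

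**The case against.** The strongest reply is that the article nowhere says incomplete cases are deleted. A repeated-measures ANOVA on imputed data could carry an intention-to-treat label, and missing-data handling is commonly left to a fuller plan. That stands as far as imputation goes, so silence on imputation is not the point. What the article does fix is the model, and that model omits baseline as a covariate.

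A reader might infer more than the documents support:

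- **That the results would describe programme completers only.** The week-10 session is planned for all participants. Someone who stops exercising but attends is included. The analysed group is those with both assessments.
- **That half the data may be missing.** The Introduction's "poor adherence, with up to 50% of participants dropping out early" concerns conventional balance and falls programmes. It is neither a forecast for this trial nor a rate of missed week-10 visits.
- **That the flow-diagram caption authorises exclusions.** "Final analysis was performed according to group allocation, noting any exclusions" is ordinary CONSORT reporting language and affirms analysis by allocation. It needs no change.
- **That the abstract promises a model the body does not deliver.** The QALY and cost section does use mixed-effects regression. It also adjusts for baseline health, so the baseline problem does not carry over to it, although a QALY from two readings still needs week 10.
- **That the effect is diluted by stoppers who gain nothing.** Such dilution depends on who attends week 10, not on the choice between these models.

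The size of the bias also rests on an assumed dropout slope in one arm only. Every bias shown in Step 3 is well below the 4-point minimally important difference that the article cites for the Functional Gait Assessment.

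**Conclusion.** The point holds in a limited form. The stated label and the stated model do not match, and the model is a poor choice for two visits. It is less precise than a baseline-adjusted analysis even with no selective dropout (SE 0.48 against 0.43), and biased when missing week-10 data relate to baseline function differently by arm. Under the stated assumptions the loss runs from nothing to about 0.5 of a true 2 points. The direction shown follows from assuming that poorer-functioning intervention participants drop out more; the opposite pattern would reverse the sign.

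No confirmatory claim depends on this. The consequence is confined to exploratory effect estimates and to the model and sample-size inputs carried into the definitive trial. Since the article says this analysis is being tried out for that trial, it is worth correcting now.

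**What to change.** In the Statistical analysis section:

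1. Replace the repeated-measures ANOVA with a baseline-conditioned model. This can be a mixed model with baseline and week 10 as outcomes and baseline means constrained equal across arms, or ANCOVA on week 10 with baseline as covariate. Adjust for site and cohort, and analyse all randomised participants in their allocated arm. The ANCOVA still needs a week-10 value, so pair it with a stated missing-data method.
2. State in Outcome measures that the week-10 assessment is also sought from participants who stop the programme.
3. Add a sensitivity analysis for missingness that depends on unseen outcomes.
4. If the ANOVA is kept, describe it as an analysis of participants with both assessments.

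The model change is a matter of wording and standard software, with no new visit or measure. The sensitivity analysis is modest extra work. Seeking week-10 data from those who stop takes some follow-up effort within a visit already planned.
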